### 8.3 Other study parameters

Binary variables will be displayed in cross-tabulations. The Person  $\chi^2$  will be used for analysis between groups.

Variables with a non-Gaussian distribution and will be analysed by means of a Mann-Whitney-U test in univariate analysis.

Statistical significance is defined as  $P < 0.05$ .

### 8.4 Interim analysis

If the DSMB requires an interim-analysis for benefit the Peto approach will be followed meaning that the study will only be stopped for beneficial effects in case of a  $P < 0.001$ . An interim analysis is performed at 105 patients. The interim-analysis is performed by the study coordinator and the epidemiologist/statistician of the DSMB together and discussed in a private meeting by only the DSMB members. If the DSMB suspects harm there will be a meeting between the DSMB, the trial research group and an independent statistician. During this meeting there should be a discussion about any potential causal relation between gastrectomy and harm based on the current literature. The final decision is made by the DSMB and their opinion is sent to the study coordinator and principal investigator. There will be no futility for this trial. The ethics committee will receive a direct copy of this advice.

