## **6.2 Randomisation, blinding and treatment allocation**

After completion of preoperative chemotherapy and signing informed consent at the outpatient clinic, participants will be randomized by means of an online random number generator, stratified by centre. Randomization will be performed by the coordinating investigator and directly provided to the participating centres. The data-analyst will be blinded for the procedure.

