## **7.5 Data Safety Monitoring Board (DSMB)**

The stop-criteria are:

- <70% complete resection without tumor residual in the proximal or distal surgical resection plane (R0) in one or both arms,
- >50% less than 10 lymph node harvested in one or both arms.

A data safety monitoring board will be assigned to evaluate the outcomes at 105 patients.

A DSMB is established to perform ongoing safety surveillance and to perform interim analyses on the safety data. This committee is an independent committee, which is composed of (names will be determined at a later stage).

None of the members have a conflict of interest with the sponsor of the study.

Criteria on which the DSMB may decide to terminate the trial prematurely:

- Clear evidence of benefit of laparoscopic gastrectomy
- Clear evidence of harm of laparoscopic gastrectomy
- External evidence, such as other trials or published data, not available during the start of this trial.

The advice(s) of the DSMB will only be sent to the sponsor of the study. Should the sponsor decide not to fully implement the advice of the DSMB, the sponsor will send the advice to the reviewing METC, including a note to substantiate why (part of) the advice of the DSMB will not be followed.

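### The study coordinator co-performs the by-arm interim analysis at 105 of 210 patients, and Sections 7.5 and 8.4 separately contradict each other on who decides and who receives the DSMB's advice

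*Protocol*

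**What the plan says.** **Timing.** Section 8.4: "An interim analysis is performed at 105 patients". Section 7.5 gives the same point: "A data safety monitoring board will be assigned to evaluate the outcomes at 105 patients". Section 4.4 plans 210 patients in total, 105 per arm.

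**Who performs the analysis.** Section 8.4: "The interim-analysis is performed by the study coordinator and the epidemiologist/statistician of the DSMB together". The result is then "discussed in a private meeting by only the DSMB members".

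**What is examined.** Section 7.5 sets two stop criteria, each applied to either arm: an R0 rate below 70%, and more than half of patients with fewer than 10 nodes harvested. Section 8.4 adds a Peto rule, P < 0.001, for stopping for benefit if the DSMB requires such an analysis.

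**Who decides and who is told.** Section 7.5: "The advice(s) of the DSMB will only be sent to the sponsor of the study". If the sponsor does not follow the advice in full, the sponsor forwards it to the METC with reasons. Section 8.4: "The final decision is made by the DSMB and their opinion is sent to the study coordinator and principal investigator", and "The ethics committee will receive a direct copy of this advice". If harm is suspected, 8.4 also provides for a meeting of the DSMB with the trial research group and an independent statistician.

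**Blinding.** Section 3 describes a non-blinded trial. Section 6.2 blinds only the data-analyst.

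**The concern.** There are two separate defects.

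The first is access. Section 8.4 closes the DSMB's discussion to outsiders, but the step before it gives an outsider the results. In an open-label trial whose primary endpoint is length of stay, knowledge of an interim difference within the trial team could affect how later patients are recruited or when they are judged fit for discharge. Keeping interim comparisons inside the DSMB removes that possibility.

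The second is authority. If the DSMB advises stopping, a reader of the protocol cannot tell whether that advice binds the sponsor, who must receive it, or whether the ethics committee hears in every case or only when the sponsor departs from the advice.

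**Working it through.** **1. Timing.** Inputs: 105 patients at the look (7.5 and 8.4 agree) and 210 planned (4.4), taking 105 as the count over both arms.

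- Fraction of the sample at the look: 105 / 210 = 0.50.
- Planned patients remaining: 210 − 105 = 105. This is a maximum, because neither section describes a pause in recruitment while data mature and are analysed.

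**2. Is the study coordinator outside the DSMB?** Yes, on 8.4's own wording: the DSMB sends its opinion to the study coordinator, alongside the principal investigator.

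**3. Can the analysis be done on pooled data?** No. Both stop criteria in 7.5 need a rate for each arm, and a P-value for benefit needs a test between arms. Whoever co-performs the work sees results by arm.

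**4. Which results?**

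- R0 rate and node harvest by arm: yes, because these are the stop criteria.
- Hospital stay by arm: only if the DSMB requires a benefit analysis. Section 8.4 makes that conditional, and 7.5 speaks of interim analyses of safety data.

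**5. Is the primary endpoint open to influence?** Section 6.1.1 ties hospital stay to adequate pain control on oral medication, a start of mobilisation, and adequate intake without intravenous fluids. These call for clinical judgement by staff who know the allocation.

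**6. Sections 7.5 and 8.4 side by side.**

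| Question | Section 7.5 | Section 8.4 |
|---|---|---|
| Who decides? | The DSMB may terminate on listed criteria, yet the sponsor may decline its advice | The DSMB, finally |
| Who receives the advice? | The sponsor only | Study coordinator and principal investigator |
| Ethics committee (METC)? | Told by the sponsor if the advice is not fully followed | Direct copy, no condition |

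No row can be satisfied under both sections as written. Section 7.5 is also unclear within itself on the first row.

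**7. Type I error.** Assume two-sided tests at 0.001 (half information) and 0.05 (end). Overall alpha = 1 − P(|Z1| < 3.29 and |Z2| < 1.96), with correlation √0.5 = 0.707, which gives about 0.0502. The issue is confidentiality and governance, not alpha.

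**The case against.** **The analysis is joint.** A reader might infer that the coordinator runs the interim alone. The text does not say so: the DSMB's statistician works alongside. That limits the coordinator's control over the analysis but not the coordinator's view of the results.

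**The team can see open-label data anyway.** Section 10.1 gives the coordinating and principal investigators the database password. That is a fair point, but possible access to records is not the same as a prepared comparison by arm for a stopping decision. The DSMB-only meeting shows that the comparison was meant to be restricted.

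**The influence on discharge is speculative.** Patients are discharged from wards in several hospitals, and nothing says that the study coordinator discharges anyone. This stands. A reader might infer that confidentiality is actually lost or the endpoint biased; the protocol shows neither.

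**The routing conflict does not cause the confidentiality gap.** This stands. The sentences on recipients concern advice, not comparative data.

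**The routing conflict is narrower than it looks.** Sections 9.5 and 10.5 pair sponsor and investigator, so sending the opinion to the principal investigator may amount to sending it to the sponsor. The decision sentence in 8.4 also follows the suspected-harm text and might apply only there. Both readings are possible. Even so, 7.5 lists harm among its termination criteria and makes no exception to its sponsor-only rule. The conflicts over the study coordinator, the ethics-committee copy and the final decision remain.

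**Harm would be handled anyway.** Section 7.1 provides for suspension pending METC review, and 7.2.2 for expedited reporting of deaths. A reader might infer that the conflict leaves a harm signal without any route; these sections show otherwise. They do not settle the standing of DSMB advice.

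**Randomisation.** Because Section 6.2 says "Randomization will be performed by the coordinating investigator and directly provided to the participating centres", a reader might infer that the person who sees interim results also controls allocation. The protocol does not say that the study coordinator and the coordinating investigator are the same person, nor that an online generator lets anyone choose or foresee an assignment.

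**Conclusion.** The point holds in two parts.

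**Access.** The plan gives a trial-team member results by arm at half the planned sample, with at most 105 planned patients still to come. This is certain for R0 rate and node harvest. For hospital stay it depends on the DSMB requiring a benefit analysis. The plan therefore does not protect the confidentiality it sets out to keep. The size of any resulting bias cannot be derived from the protocol, and no leak is shown.

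**Authority.** Sections 7.5 and 8.4 cannot both be followed on the decision-maker, the recipients, or the condition for informing the ethics committee. This is a contradiction in current text and needs no assumption beyond reading both sections as in force. It is a governance defect independent of the first part.

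**What to change.** **Section 8.4, access.** State that the DSMB's statistician alone prepares the by-arm interim analysis, and that the study coordinator supplies the data without arm summaries. Keep the DSMB-only meeting.

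**Section 8.4, suspected harm.** State what comparative data, if any, the trial research group may see at that meeting. Otherwise it remains a second, unregulated route to interim results.

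**Sections 7.5 and 8.4, authority.** Write one rule into both: who makes the final decision, who receives the DSMB's output, and whether the ethics committee always gets a direct copy or hears only when the sponsor departs from the advice. Either existing arrangement can be made consistent; the sponsor should choose one and remove the other, and also settle the ambiguity within 7.5.

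**Cost.** Wording in two sections. The DSMB's statistician is already assigned to the analysis. The small downside is that this person does the by-arm work alone. The sample size, the timing of the look and the P < 0.001 rule stay as they are.

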## 9. ETHICAL CONSIDERATIONS

### 9.1 Regulation statement

This study will be conducted according to the principles of the Declaration of Helsinki (2008) and in accordance with the Medical Research Involving Human Subjects Act (WMO).

### 9.2 Recruitment and consent

Patients are recruited to participate in this trial at the outpatient clinic. They are introduced to the study by a sub-investigator who will not be involved in the care and treatment of the patient but who is part of the study team and therefore can inform the patient about the study and answer the questions of the patient. The subjects will be fully informed about the study by means of a patient information letter that explains the trial. Potential participants can contact the coordinating investigator or independent physician for any questions concerning the trial. The subjects will be given a week to consider their

decision. The informed consent form will be signed by both the participant and the investigator. The patient information brochure and the informed consent form are attached (appendix 5)

### **9.3 Objection by minors or incapacitated subjects (if applicable)**

Not applicable

### **9.4 Benefits and risks assessment, group relatedness**

All surgical techniques used in this research are known to be safe.

### **9.5 Compensation for injury**

The sponsor/investigator obtained dispensation from the statutory obligation to provide insurance from the Medical Ethics Committee UMC Utrecht. The reason for dispensation is that if a study includes two different, but commonly used procedures, the insurance does not cover damage caused by the study.

### **9.6 Incentives (if applicable)**

Not applicable

## **10. ADMINISTRATIVE ASPECTS, MONITORING AND PUBLICATION**

### **10.1 Handling and storage of data and documents**

The subjects will be coded by patient number in order to handle personal information about patients anonymously. The patient's information will solely be available to this research group by the use of SPSS guarded with a password. The coordinating investigator and the principal investigator know this password. The data will be kept for 15 years. This will be done in concordance with the Dutch Personal Data Protection Act (Wet Bescherming Persoonsgegevens, WBP)

### **10.2 Monitoring and Quality Assurance**

The study is classified as a low risk study (verwaarloosbaar risico) and will be monitored accordingly. For details, see monitoring plan.

### **10.3 Amendments**

Amendments are changes made to the research after a favourable opinion by the accredited METC has been given. All amendments will be notified to the METC that gave a favourable opinion.

### **10.4 Annual progress report**

The investigator will submit a summary of the progress of the trial to the accredited METC once a year. Information will be provided on the date of inclusion of the first subject, numbers of subjects included and numbers of subjects that have completed the trial, serious adverse events/ serious adverse reactions, other problems, and amendments.

### **10.5 End of study report**

The investigator will notify the accredited METC of the end of the study within a period of 8 weeks. The end of the study is defined as the last patient's last visit.

In case the study is ended prematurely, the investigator will notify the accredited METC within 15 days, including the reasons for the premature termination.

Within one year after the end of the study, the investigator/sponsor will submit a final study report with the results of the study, including any publications/abstracts of the study, to the accredited METC.

## **10.6 Public disclosure and publication policy**

Not applicable

## 11. Appendices

### 11.1 Appendix 1

### Postoperative morbidity and mortality

- Anastomotic leakage
- Anastomotic stricture
- Respiratory complications
- Cardiac complications
- Intra-abdominal bleeding
- Intra-abdominal abscess
- Sepsis
- Ileus
- Wound infection
- Fistula
- Urinary tract infection
- Dumping syndrome
- Mortality

All complications will be defined according to the Esophageal Complications Consensus Group. All complications will be scored according to the modified Clavien-Dindo classification and the Comprehensive Complication Index.

**11.2 Appendix 2****Quality of Life questionnaires**

- EQ-5D-5L
- EORTC QLQ-30
- EORTC QLQ-STO22

## 11.3 Appendix 3

## Cost-effectiveness questionnaires

- SF-HLQ

Instructie

Deze vragenlijst gaat over de gevolgen van gezondheidsproblemen voor betaald werk en onbetaald werk (bijv. huishoudelijk werk). Deze vragen hebben steeds betrekking op de afgelopen 4 weken. Met gezondheidsproblemen worden zowel uw lichamelijke als uw emotionele problemen bedoeld.

## 1. Hebt u momenteel betaald werk?

☐ Nee (*gaat u door naar vraag 9*)

☐ Ja

Voor hoeveel uur per week hebt u een aanstelling? ..... uren per week  
 Over hoeveel dagen zijn deze uren verdeeld? ..... dagen  
 Wat is uw beroep? .....

## 2. Hebt u de afgelopen 4 weken verzuimd van betaald werk vanwege gezondheidsproblemen?

☐ Nee

☐ Ja, ik heb ..... werkdagen verzuimd

☐ Ja, ik heb ..... werkdagen verzuimd, maar ik heb hiervan wel .... dagen op  
 arbeidstherapeutische basis gewerkt

Hebt u langer dan de gehele afgelopen 4 weken verzuimd van betaald werk vanwege gezondheidsproblemen?

☐ Nee

☐ Ja, ik heb me ziek gemeld sinds .....(*gaat u door naar vraag 8*)

Mensen met gezondheidsproblemen moeten daarvoor soms verzuimen van hun werk. Het kan echter voorkomen dat iemand wel op zijn werk aanwezig is (eventueel op arbeidstherapeutische basis), maar zijn werk minder goed doet vanwege gezondheidsproblemen, daarover gaan de vragen 3 t/m 7.

3. Werd u de afgelopen 4 weken op uw betaald werk gehinderd door gezondheidsproblemen?

- ☐ Nee, in het geheel niet (*gaat u door naar vraag 6*)
- ☐ Ja, een beetje
- ☐ Ja, heel erg

4. Hoeveel dagen in de afgelopen 4 weken hebt u wel betaald werk verricht (eventueel op arbeidstherapeutische basis), terwijl u last had van gezondheidsproblemen?

..... dagen (*de dagen waarop u helemaal niet hebt gewerkt, omdat u zich ziek hebt gemeld hoeft u niet mee te rekenen*)

5. Wilt u aangeven hoe goed u hebt gewerkt op de dagen waarop u wel op uw werk was terwijl u last had van gezondheidsproblemen.  
(Een 1 betekent dat u zeer slecht in staat was uw werk uit te voeren en een 10 betekent dat uw werk niet werd beïnvloed.)

|                          |                          |                          |                          |                          |                          |                          |                          |                          |                          |
|--------------------------|--------------------------|--------------------------|--------------------------|--------------------------|--------------------------|--------------------------|--------------------------|--------------------------|--------------------------|
| 1                        | 2                        | 3                        | 4                        | 5                        | 6                        | 7                        | 8                        | 9                        | 10                       |
|  |  |  |  |  |  |  |  |  |  |
| zeer slecht              |                          |                          |                          |                          |                          |                          |                          |                          | even goed als normaal    |

6. Nu volgt een aantal uitspraken die voor mensen met gezondheidsproblemen van toepassing kunnen zijn met betrekking tot betaald werk. Geef aan hoe vaak elke uitspraak op u van toepassing was in de afgelopen 4 weken

Ik was wel op mijn werk, maar als gevolg van gezondheidsproblemen .....

|                                                | bijna
nooit           | soms                     | vaak                     | bijna
altijd          |
|------------------------------------------------|--------------------------|--------------------------|--------------------------|--------------------------|
| had ik concentratiestoornissen                 |  |  |  |  |
| moest ik in een langzamer tempo werken         |  |  |  |  |
| moest ik mij afzonderen                        |  |  |  |  |
| had ik meer problemen om beslissingen te nemen |  |  |  |  |
| moest ik werk uitstellen                       |  |  |  |  |
| moest ik werk laten overnemen door anderen     |  |  |  |  |
| had ik andere problemen, nl: .....             |  |  |  |  |

7. Als u het werk zou moeten inhalen dat u in de afgelopen 4 weken niet hebt kunnen verrichten vanwege uw gezondheidsproblemen, hoeveel uur zou u dan moeten werken?

..... uur (de dagen waarop u helemaal niet hebt gewerkt, omdat u zich ziek hebt gemeld hoeft u niet mee te rekenen)

8. Wat is uw eigen netto inkomen uit betaald werk?  
(Het gaat om het gedrag dat u 'schoon' in uw handen krijgt. Voor alle duidelijkheid: het gaat alleen om uw eigen inkomen, dus zonder dat van uw eventuele partner)

- ☐ € ..... per week
- ☐ € ..... per 4 weken
- ☐ € ..... per maand
- ☐ € ..... per jaar
- ☐ Weet ik niet / wil ik niet zeggen

9. Welke van de volgende situaties is op u van toepassing? Indien meerdere situaties van toepassing zijn, wilt u dan aangeven welke situatie het meest op u van toepassing is.

- ☐ Ik heb een betaalde baan
- ☐ Ik zorg voor het huishouden (en eventueel kinderen)
- ☐ Ik ben gepensioneerd of met prepensioen
- ☐ Ik ben scholier of student
- ☐ Ik kan (gedeeltelijk) geen betaald werk doen vanwege gezondheidsproblemen en ben voor .....% arbeidsongeschikt
- ☐ Ik doe geen betaald werk om andere redenen  
(Bijv. vanwege onvrijwillige werkloosheid of vrijwilligerswerk)

10. Hebben anderen in de afgelopen 4 weken huishoudelijke taken die u normaal wel doet overgenomen in verband met gezondheidsproblemen?

- ☐ Nee
- ☐ Ja, namelijk (meerdere antwoorden mogelijk)
- ☐ gezinsleden voor ..... uur
  - ☐ andere onbetaalde mensen voor ..... uur
  - ☐ thuiszorg voor ..... uur
  - ☐ andere betaalde hulp voor ..... uur

- Health care use questionnaire

NL47444.041.14

LOGICA trial

www.logica-trial.nl

### Vragenlijst zorggebruik

Hoe vaak bent u de **afgelopen 6 weken**:

- |                                                       |             |
|-------------------------------------------------------|-------------|
| 1. bij de huisarts geweest?                           | ..... maal  |
| 2. op de spoedeisende hulp of huisartsenpost geweest? | ..... maal  |
| 3. op de polikliniek in het ziekenhuis geweest?       | ..... maal  |
| 4. opgenomen geweest in het ziekenhuis?               | ..... maal  |
| a. Hoeveel dagen was dit in het totaal?               | ..... dagen |

Waar verbleef u de **afgelopen 6 weken**:

- |                      |                            |
|----------------------|----------------------------|
| 5. Thuis:            | Niet / Altijd / .... Dagen |
| 6. Revalidatieplek   | Niet / Altijd / .... Dagen |
| 7. Verpleeghuis      | Niet / Altijd / .... Dagen |
| 8. Overig, namelijk: |                            |
| a. ....              | .... Dagen                 |
| b. ....              | .... Dagen                 |
| c. ....              | .... Dagen                 |

Heeft u de **afgelopen 6 weken**:

- |                                                        |                          |
|--------------------------------------------------------|--------------------------|
| 9. Hulp in huis gehad van thuis-, buurt- of mantelzorg | Nee / Ja,                |
| a. Indien ja, hoe vaak?                                | .... maal per week / dag |

## Appendix 4 VAS score

### Belasting van de operatie:

1. Kunt op deze schaal aangeven hoeveel pijn u nu heeft?  
U doet dat door een kruisje (X) te zetten tussen geen pijn en heel veel pijn.

Geen pijn \_\_\_\_\_ Heel veel pijn

2. Kunt u op deze schaal aangeven hoeveel pijn u nu heeft ter plaatse van de operatiewonden?  
U doet dat door een kruisje (X) te zetten tussen geen pijn en heel veel pijn.

Geen pijn \_\_\_\_\_ Heel veel pijn

3. Hoe hinderlijk is nu voor u de pijn van de operatiewonden?  
Graag het hokje van uw keuze aankruisen

- ☐ niet  
☐ een beetje  
☐ nogal  
☐ heel erg

4. Wij willen graag weten hoe belastend, al met al, de behandeling voor u is geweest? Zou u op de lijn hieronder willen aangeven hoe belastend u het vond?  
U doet dat door een kruisje (X) te zetten tussen helemaal niet belastend en heel erg belastend.

Helemaal niet belastend \_\_\_\_\_ Heel erg belastend

5. In hoeverre vindt u dat de behandeling de moeite waar is geweest?  
Graag het hokje van uw keuze aankruisen

- ☐ niet  
☐ een beetje  
☐ nogal  
☐ heel erg

6. Indien u nu voor de keuze zou staan, zou u dan voor dezelfde behandeling kiezen?  
Graag het hokje van uw keuze aankruisen.

- ☐ ja  
☐ nee  
☐ ik weet niet

Zo nee, kunt u aangeven waarom niet? .....

